# Rural trauma team development training amongst medical trainees and traffic law enforcement professionals in a low-income country: a protocol for a prospective multicenter interrupted time series

**DOI:** 10.1097/SP9.0000000000000013

**Published:** 2024-02-08

**Keywords:** Africa, intervention, rural trauma, team development, team training, trauma teams

## Abstract

**Background::**

Road traffic injuries and their resulting mortality disproportionately affect rural communities in low-middle-income countries (LMICs) due to limited human and infrastructural resources for postcrash care. Evidence from high-income countries show that trauma team development training could improve the efficiency, care, and outcome of injuries. A paucity of studies have evaluated the feasibility and applicability of this concept in resource constrained settings. The aim of this study protocol is to establish the feasibility of rural trauma team development and training in a cohort of medical trainees and traffic law enforcement professionals in Uganda.

**Methods::**

Muticenter interrupted time series of prospective interventional trainings, using the rural trauma team development course (RTTDC) model of the American College of Surgeons. A team of surgeon consultants will execute the training. A prospective cohort of participants will complete a before and after training validated trauma related multiple choice questionnaire during September 2019-November 2023. The difference in mean prepost training percentage multiple choice questionnaire scores will be compared using ANOVA-test at 95% CI. Time series regression models will be used to test for autocorrelations in performance. Acceptability and relevance of the training will be assessed using 3 and 5-point-Likert scales. All analyses will be performed using Stata 15.0. Ethical approval was obtained from Research and Ethics Committee of Mbarara University of Science and Technology (Ref: MUREC 1/7, 05/05-19) and Uganda National Council for Science and Technology (Ref: SS 5082). Retrospective registration was accomplished with Research Registry (UIN: researchregistry9490).

## Introduction

HighlightsInjury-related mortality significantly impact low-middle-income countries.Rural trauma teams could improve the efficiency of injury care in low-middle-income countries.This study will assess the effect of rural trauma team development course training, viewing medical trainees, and traffic police as potential human resources for health.The results could inform the implementation of future trauma teams in rural settings.

Trauma is a public health threat, which claims an annual death toll of 4.5 million lives globally, contributing to 10% of global disease burden^1^. Over 90% of global deaths due to trauma disproportionately occur in low- and middle-income countries (LMICs) such as those in sub-Saharan Africa where trauma life support educational programs are scarce^1^. The main cause of trauma related deaths in Africa are road traffic crashes^2^. Notwithstanding injury prevention being on top of the agenda for the African Centers for Disease Control, Africa records the highest road traffic crash fatality rates (26.6 per 100 000 population) amongst the WHO regions, which is nearly triple that of Europe at 9.3 per 100 000^3^. According to Lagarde^4^, sub-Saharan Africa contributes to 10% of the global burden of road traffic crash fatalities despite disproportionately owning only 4% of the world’s motorized vehicles.

Several factors contribute to higher postcrash fatalities in LMICs, including limited: infrastructural, financial, physical, and human resources^5^. According to the recent WHO (2023) alert on safeguards for health worker recruitment^5^, it turned out that 67.3% (37 of 55) vulnerable countries for shortage of health workers were from the African region, implying Africa’s obvious slow progress to achieving the sustainable development goal target for universal health care coverage by 2030. For instance, a study that evaluated surgical capacity in three African countries found that nurses and medical assistants performed surgical procedures as opposed to surgeons^6^. However, such ‘task-shifting’ without capacity building through skills-training could have a negative impact on treatment outcomes. Moreover, according to the WHO Fifth Global Forum on Human Resources for Health held in (2023), the deficit of skilled workforce in Africa is anticipated to be exacerbated by the accelerated exodus of health professionals due to COVID-19 related international recruitment, further crippling the fragile health systems^5^.

## Rationale for rural trauma team development and training in Uganda

Uganda is one of the countries whose universal health care coverage index is below 55 and is on WHO, 2023 safeguard list^5^. Furthermore, Uganda has no formal prehospital care systems thus the majority of patients who sustain trauma arrive at hospitals by public means or by police cars without receiving any primary care, which may exacerbate their injury severity^7^. In addition, the country has a health workforce to population density ratio of 1: 25 000 far below the global median of 49 per 10 000 people^5^. For instance, a study of 72 hospitals in western Uganda revealed that there were only 0.7 surgeons for every 100 000 population and that mostly anesthesia was provided by nonphysician anesthetists^8^. As such, barely any of the Ugandan assessed hospitals met the minimum WHO staffing standards for essential surgery^9^.

Evidence from systematic reviews show that the lack of sustainable expertise for injury care and inadequate skill-based training of first responders contributes to higher injury-related mortality in LMICs^10^. Reliably trained and motivated staff are key elements of effective trauma systems^11^, but are inadequate in LMICs^12^. There have been efforts from WHO to design a mentorship program for violence and injury prevention (Mentor-VIP) to address the human resource capacity for health in LMICs^13^, but this largely targets qualified public health practitioners and established researchers as opposed to clinicians in practice and trainees such as medical interns who make the first contact with injured patients in LMICs. Moreover, task-shifting was identified as one of the options to boost human resource workforce in the health sector of LMICs^14^ but the potential role of medical trainees and traffic police as ‘sustainable human resources for health in the trauma context’ has been underexplored. Several trauma care educational modules have been piloted in LMICs to address the unmet human resource needs but their impact assessment has largely been theoretical without the skills component^15^. Moreover, other than the ongoing clinical trial on the effect of advanced life support and primary trauma courses in India^1^, such trauma education programs have not been validated in randomized controlled settings, which could have affected their clinical application^16^.

Uganda has a 6-year long undergraduate medical curriculum. The curriculum has two preclinical and four clinical years, one of which is an internship year taken outside the university setting as a prerequisite for full medical licensure. During the clinical attachment, trainees complete 1–5 months of supervised rotations in major departments, including but not limited to; surgery and traumatology, obstetrics and gynecology, internal medicine, and pediatrics. In principle these medical trainees provide the first contact with trauma patients. As such, they complete patients’ admission, initiate emergency resuscitation, discuss case management amongst themselves (horizontal consultation) before consulting with senior faculty, and may discharge or coordinate patients’ referrals. In the face of scarce human resources, it is therefore considered that incorporating these trainees into trauma teams under guidance with ‘pre-and in-service’ skills-training, could formulate consistently structured-priority-driven injury care. Research in Sweden shows that interns are underutilized powerful catalyzers for medical learning, and for taking responsibility in patients care pathways^17^.

There have been efforts to incorporate an advanced trauma life support course (ATLS) of the American College of Surgeons^18^ in Ugandan medical curricula, however, the content remains theoretical without being conceptualized to suit the country’s resource limited settings. In addition, ATLS in its patented form is arguably expensive for medical trainees in LMICs. To-date, Uganda does not have any certification center for this program, requiring one to travel overseas to attain this valuable training. There were further efforts to scale out an alternative level III targeted primary trauma courses in Uganda^19^, when it demonstrated its potential in skill improvement in India^20^, but the course failed due to lack of international accreditation and recognition for global job markets in addition to its minimal reported impact on mortality reduction^16^. The more applicable, internationally recognized rural trauma team development course (RTTDC) of the American College of Surgeons^21^ has demonstrated its potential in minimizing morbidity and mortality amongst a general trauma population^22^, but has largely been evaluated in middle and high-income countries^23^.

According to the Uganda police annual traffic report (2017), 78% of fatal road traffic injuries occur in rural regions where doctors are scarce and where police ambulances are the most accessible^24^. The Ugandan Ministry of Health and Medical Schools purposively deploy medical trainees in such rural regional referral hospitals (Level III trauma centers) partly to address the human resource needs, and to accelerate the trainees’ ‘hands-on’ experience. Therefore, building capacity for rural trauma training to the traffic law enforcement professionals who undertake the role of prehospital emergency evacuation of injured patients from rural regions and to medical trainees who provide the first hospital-based emergency care would positively impact the consequences of injuries in such environment^22^. However, the inception, implementation, and outcome impact of rural trauma team development training in such settings is poorly documented. To the best of the authors’ knowledge, Ugandan studies, which have evaluated the applicability and impact of such an intervention are scarce. In this study, undergraduate medical trainees and traffic police are considered potential human resources for trauma care.

## Study objectives

### Main objective

The main objective of this study is to evaluate the feasibility of rural trauma team development training amongst medical trainees and road traffic law enforcement professionals, using the RTTDC of the American College of Surgeons^18^ as a starting point. This research is nested in a broader ongoing trial on the use of allied health and law enforcement trauma registries for motorcycle related injuries in Uganda (Pan African Clinical Trial Registry No. PACTR202308851460352). The target course participants were chosen for this intervention because they are often the first responders in trauma care in Uganda’s resource constrained settings.

### Specific objectives

To compare the pre-RTTDC and post-RTTDC training scores amongst medical trainees.To determine the relevance and acceptability to promulgation of RTTDC amongst medical trainees and traffic law enforcement professionals in Ugandan rural level III trauma centers.

### Hypotheses

The null hypothesis of this research protocol is that there is no difference in pre interventional and postinterventional training scores of research participants.

## Methods

### Study design

This protocol describes a multicentre interrupted time-series of interventional training in a prospective cohort of medical trainees and traffic law enforcement professionals during 28th September 2019–28th November 2023. There were temporal delays in the publication of this protocol due to the prioritization of COVID-19 related protocols and studies during the commencement period. This protocol was developed in accordance with the (STROCSS, 2021) guidelines for strengthening the reporting of cohort, cross-sectional, and case–control studies in surgery^25^; and in line with guidelines for reporting evidence-based practice educational interventions and teaching (GREET)^26^.

### Source of data and study settings

This study will be conducted at three regional referral and teaching hospitals in Uganda, including Kiryandongo, Jinja, and Hoima. These facilities have similar characteristics in the sense that they all serve as internship and residency sites for graduating general doctors, surgery residents and as teaching sites for the Kampala International University Medical School. In co-operation with local surgeon consultants, each of these tertiary hospitals offers specialized services including emergency surgery for injured patients such as those with neuro, orthopedic, and general trauma. The key staff in the surgery and trauma departments include at least a specialist surgeon, a master’s resident, intern doctor/nurse and support staff who work with other departments such as occupational therapy, physiotherapy, and rehabilitation to offer 24 h multidisciplinary services to the injured patients. In addition, each of these facilities receive undergraduate medical trainees including those studying for Bachelor of Medicine and Bachelor of Surgery, Bachelor of Nursing Sciences, and Bachelor of Clinical Medicine degrees here being collectively referred to as medical trainees. The trainees rotate on a 1–5 months basis in major clinical disciplines such as surgery amongst others. Furthermore, each of these hospitals are in proximity with the regional district police headquarters which offers complementary services such as legal guidance on traffic crashes, third party compensation claims and issuance of ‘police form 3A’ for the examination of injured persons. Patients sustaining either intentional or unintentional injuries are immediately encouraged to report to the police for investigations and often police attend to such patients as first-responders at the crash scenes.

### Scope of the study training

The rural trauma team development course was developed by the committee on trauma of the American College of Surgeons (https://www.facs.org/quality-programs/trauma/education/rural-trauma-team-development-course/) to help rural health facilities improve on the quality of injury care and trauma outcome. It was designed on the basis that in most situations, rural facilities can form an organized efficient core response team consisting of at least three members, for example, doctor (team leader), allied health professional (such as a medical intern or nurse), and paramedic (rescue traffic police in Ugandan settings) to address the healthcare needs of an injured patient.

This face-to-face training will entail a brief introduction to rural trauma systems, pretest questionnaire regarding pre-existing knowledge about the subject matter, essentials of prehospital communication to receiving hospitals and safe transportation of a trauma patient (targeted for traffic police who often undertake this role in the Ugandan context). Furthermore, we shall organize participants in teams of five with specific roles such as team leader or member, identify local resources and limitations, and demonstrate resuscitation of trauma patients through simulated case scenarios with locally available: resuscitation equipment, mannikins, radiographs, PowerPoint projections, and videos. The efforts throughout the training will endeavor to demonstrate to participants a sequential approach to trauma, that is, primary survey, decision to transfer, secondary survey, and process improvement by use of clinical case scenarios.

Subsequently, teams will be tasked to manage trauma case scenarios during which they will be observed for the following skills. First, to perform a primary survey to demonstrate assessment and interventions for airway compromise with emphasis on skills for manual airway maneuvers. Secondly, to demonstrate teamwork, leadership, and communication skills in making timely decision to consult senior faculty or transfer. Thirdly to execute secondary survey and demonstrate assessment for respiratory distress, quality of ventilation, oxygen administration, chest-tube and needle thoracotomy, 3-way occlusive dressing, detection of shock, control of external hemorrhage with compression or tourniquet, fracture splintage, and spine immobilization for safe transfer, detection of deteriorating level of consciousness, and clinical signs of raised intracranial pressure. Lastly, to provide peer review, audit team performance, and suggest areas for improvement to increase patients’ safety with particular attention on how the team’s approaches would differ in special trauma populations such as pediatrics, elderly, and pregnant women.

Participants will be given expert feedback on their team performance regarding case scenarios. First, based on the assigned skilled team member roles as per the 4th edition of RTTDC^27^. Secondly, based on the trauma nontechnical skills scale (T-NOTECHS)^28^. The (T-NOTECHS) scale rates team performance based on five domains including leadership; co-operation and resource management; communication and interaction; assessment and decision-making, and situation awareness and coping with stress. Each domain will be evaluated on a Likert scale of 1–5 where 5 represents an ideal flawless team performance whereas 1 indicates performance that did not demonstrate teamwork behavior as described by Steinemann *et al*.^28^. This tool has been validated and found to be reliable for evaluation and measurement of nontechnical skills during training of trauma teams^29^. In return, participants will give their immediate feedback on the training through a structured postcourse evaluation form and complete the post-training trauma based multiple choice questionnaires (MCQs) at 3 months follow-up. The training and assessments will be conducted in English which is the official language of instruction in Uganda.

### Training procedure, team construct, and course implementation

On average 12 (6–24) training sessions will be conducted per site between 28th of September 2019 and 28th of November 2023. Cohorts of participants will be enrolled every after 3 months to strike a balance between the average duration of surgical internship deployment by the Ugandan ministry of health which lasts 1–5 months, and the surgery clinical rotations for medical students which lasts 2 months. Furthermore, the effects of the training are presumed to ‘decay’ after this period and the authors project to realize the targeted sample size based on the 3 months interval. However, permission will be sought from the ethical committee to extend the study in case the target sample is not obtained during the approved duration of the study. The mode of delivery and content of the RTTDC training will not be modified. The training will be advertised by hospital administrators and class representatives and eligible participants will be recruited based on first come first serve. The training dates will be selected to suit the designated days for clinical grand rounds and/ or continuous professional development sessions so as not to interfere with the university and hospital daily schedules. The investigators will use student unique numbers from university hospital administrators’ database to randomly assign recruited participants into teams and to ensure that each participant is recruited once. The participating law enforcement professionals who will show up for the training will pick ballot papers randomly to be assigned to the already created medical trainee teams. The chief trainer will be a chief surgeon (HL) who attended the RTTDC instructor course. The surgeon will coach two co-trainers who are master of surgery residents undertaking a traumatology rotation, at the participating hospitals to make a total of three trainers. Since the program is aimed at capacity building, and residents directly supervise interns in Uganda, the research and ethics board approved training of residents as opposed to consultants not to over strain the skeleton specialized staff at the study sites. Interns and residents contribute to 75% of the health workforce in public hospitals in Uganda^8^. The program will be designed for two days, targeting 30 participants with a trainer: trainee ratio of 1:10, which is the maximum permissible for each training session according to the committee on trauma of the American college of Surgeons. For each team task, participants will be grouped into teams of five to role play a surgeon, surgeon assistant/intern, an anesthesiologist/anesthetic assistant, an allied health professional (emergency room nurse/laboratory/imaging personnel), and a rescue police (representing paramedics in Uganda’s settings).

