### Sample size estimation

According to the respective hospital administrators, a total of 1500 medical trainees had been received at the three participating hospitals during the academic year 2018/2019, which preceded the study. Using the hypergeometric formula in equation 1 for determining sample size in smaller populations,

(1)
$$n=\frac{Nz^{2}\mathrm{pq}}{\left[E^{2}\left(N-1\right)+z^{2}\mathrm{pq}\right]}$$

where:

*N* (population size) =1500

Z=1.96 assuming 95% CI.

P and Q are population proportions that will approve or disapprove the promulgation of rural trauma team development training, each assumed to be 50% since these proportions are unknown

E=value of accuracy of the sample proportions (alpha= 0.05) at 95% CI

*n* (sample size)=307. Since, we plan to retain this same cohort of trainees after 3 months of follow-up for purposes of their incorporation into real-world rural trauma teams during the second phase of the project which will run for the next 4 years from the time of postcourse evaluation, and with a projected 10.25% annual loss to follow-up and nonresponse, we shall add 41% to increase internal validity for the entire 4-year period, thus the final minimum sample size for medical trainees will be 433.

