### Sampling methods

For proportionate representation, the proportion ‘p’ will be computed as shown in equation 2, depending on the number of medical trainees each hospital received during the year that preceded the study.

(2)
$$p=\mathrm{sample}\left(n\right)x\frac{100}{\mathrm{Population}\left(N\right)},$$

This means that ~26.7% of each hospital’s annual trainees intake will be recruited, resulting in 321 participants from Kiryandongo, 65 from Jinja, and 47 from Hoima regional referral hospitals.

For the case of law enforcement professionals, the selection will be purposive where the regional police in-charge of traffic will be asked to nominate 22 participants, which is approximately the average number of serving officers at the headquarters for each region, totaling to 66, targeting police stations on main highways leading to the respective municipalities where the study sites are located. Those who consent to participate will then be randomly assigned to join the medical trainee teams. The assignment will be that only 1–2 traffic officers attend a particular training until the required number is attained so as not to strain the police workforce.

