### Study strengths and limitations

There will be some limitations in this study. First, our trauma team simulation with traffic police and students in medical training could arguably differ from the physician-led emergency medical teams in affluent Western countries, consequently limiting the generalizability of our results to LMICs. Secondly, regarding training for police, we hope to emphasize the key communication aspects of evacuation and prehospital safe transportation of injured patients to hospitals. As such, we shall not assess the trauma knowledge based MCQ for law enforcement participants on assumption that they have no pre-existing clinical exposure but information on their trauma nontechnical skills and applicability of the gained knowledge to their work environment will be obtained. Furthermore, medical trainee participants’ knowledge could change with time irrespective of the intervention but we hope that having multiple interrupted time series of intervention sessions at multiple study sites and using time series autoregression models will overcome this obstacle in addition to limiting confounding due to between group differences^38^. Lastly, the mean difference in prepost training MCQs for medical trainees might only depict knowledge improvement which does not necessarily transform to clinical skills that impact patient outcomes. However, the authors plan to transfer this classroom knowledge into clinical practice in a cluster randomized controlled trial to determine whether the apparent knowledge changes during the training are not due to other interventions, impact on clinical time efficiency, and patient outcomes in our constrained resource context.

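### Session size, sessions per site and trainee quotas do not multiply out, so the multi-site time series the protocol relies on is not secured

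*Protocol article*

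**What the plan says.** Three sections of the protocol article fix the number of time points per site.

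- *Training procedure, team construct, and course implementation* gives the number of sessions: "On average 12 (6–24) training sessions will be conducted per site between 28th of September 2019 and 28th of November 2023". It gives the interval: "Cohorts of participants will be enrolled every after 3 months". It gives the session size: "targeting 30 participants with a trainer: trainee ratio of 1:10, which is the maximum permissible for each training session". Places are allocated in order of arrival: "eligible participants will be recruited based on first come first serve".
- *Sample size estimation* sets the total: "thus the final minimum sample size for medical trainees will be 433".
- *Sampling methods* divides that total by hospital, "resulting in 321 participants from Kiryandongo, 65 from Jinja, and 47 from Hoima regional referral hospitals", and adds 22 traffic officers per region (66 in all), of whom only one or two attend any one training.

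Two further sections use the resulting series. *Statistical analysis* plans ARIMA models of test performance over the study period by trainee group. *Study strengths and limitations* concedes that trainees' knowledge may change over time regardless of the training, and offers as the remedy "having multiple interrupted time series of intervention sessions at multiple study sites" together with autoregressive models.

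**The concern.** The sessions at a site are the points of its time series. The article gives four figures that bear on that number (sessions per site, interval, session size, quota), and they do not agree for two of the three hospitals.

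The pooled comparison of scores before and after training does not depend on the session plan. The defence against change over time does. It needs usable series at more than one hospital; with only a few points, or points resting on a handful of trainees, a pattern seen at Kiryandongo cannot be checked elsewhere. If the mix of hospitals also shifts over the study period, a difference between hospitals can look like a trend in calendar time.

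**Working it through.** **Inputs.** Sessions per site 12 (6–24), interval 3 months, session size 30, and window 28 September 2019 to 28 November 2023 (*Training procedure*). Quotas 321 / 65 / 47, police 22 per site, 1–2 officers per session (*Sampling methods*). Total 433 (*Sample size estimation*).

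**The plan's own total.** The finite-population formula with N = 1500, z = 1.96, p = q = 0.5 and E = 0.05 gives 1440.6 / (3.7475 + 0.9604) = 306.0, against a stated 307. Then 307 × 1.41 = 432.9, or 433, and 321 + 65 + 47 = 433. The quotas agree with the stated total.

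**Reading A: sessions reach 30.** Sessions needed = quota / 30, rounded up.

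| Site | Trainees only | With 22 police |
|---|---|---|
| Kiryandongo | 321/30 = 10.7, so 11 | 343/30 = 11.4, so 12 |
| Jinja | 65/30 = 2.2, so 3 | 87/30 = 2.9, so 3 |
| Hoima | 47/30 = 1.6, so 2 | 69/30 = 2.3, so 3 |

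The stated minimum of 6 sessions would be 6 × 30 = 180 places per site, against 87 people at Jinja and 69 at Hoima. The stated average gives 3 × 12 × 30 = 1080 places for 433 + 66 = 499 people, 2.2 times as many as needed. Only Kiryandongo fits: 12 × 30 = 360 places for 343 people.

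**Reading B: 30 is a ceiling.** Trainees per session = quota / sessions.

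| Site | 6 sessions | 12 sessions |
|---|---|---|
| Kiryandongo | 53.5 (above the ceiling) | 26.8 |
| Jinja | 10.8 | 5.4 |
| Hoima | 7.8 | 3.9 |

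Twelve sessions per site now fit. The models are planned by trainee group, and *Statistical analysis* names three cadres. If these were evenly spread, Hoima would have 3.9 / 3 = 1.3 trainees per cadre per session.

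**Interval.** The window is 50 months. Sessions at months 0, 3, …, 48 give 17 slots, or 16 if the 3-month test must also fall inside the window. Twelve sessions span 11 × 3 = 33 months and fit. Twenty-four span 23 × 3 = 69 months and do not fit at one session per cohort, whichever way 30 is read.

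**Share of the data.** Kiryandongo supplies 321 / 433 = 74% of trainees on either reading.

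**Illustration only.** Suppose all sites start together and fill 30 trainee places each quarter. The first round is 30 / 30 / 30, so Kiryandongo's share is 33%. The second is 30 / 30 / 17, so its share is 30 / 77 = 39%. The third is 30 / 5 / 0, and every later round is Kiryandongo alone. The article states no such calendar.

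**The case against.** The strongest reply is that the article calls 30 the maximum as well as the target. Read as a maximum, the average of 12, the 3-month interval and the quotas are compatible. The police rule supports this reading: seating 22 officers at one or two per session takes 11 to 22 sessions per site, close to the stated average, whereas 2–3 sessions would seat only 2 to 6. This stands. It means that Reading A is not the only reading, and that the four figures are not irreconcilable as a whole. It does not remove the difficulty, because the target of 30 is then given up at two sites and their points rest on about four or five trainees each.

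Four other points deserve an answer.

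- The limit on 24 assumes one session per cohort, which the article does not say. This is fair. If a cohort is split over several sessions, 24 can be reached, but sessions are then no longer separate quarterly time points.
- The range 6–24 may run across sites, so nothing assigns 6 to Kiryandongo. A reader might infer that the plan is impossible there; it is not, since 12 sessions fit. A range across sites still leaves Jinja and Hoima below its lower end on Reading A.
- The 433 is a minimum. But six full sessions at Hoima would need 180 − 22 = 158 trainees against a quota of 47, which would undo the proportionate allocation.
- A site term in the models can be left to an analysis plan. Agreed: its absence from the article is not counted as an error here. It is part of the remedy.

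**Conclusion.** The two sections do not multiply out and need reconciling. If sessions reach 30, Jinja and Hoima give 2–3 points each, below the stated minimum of 6. If 30 is a ceiling, at 12 sessions they give points of about 5 and 4 trainees. The upper limit of 24 does not fit the window at one session per cohort. On either reading Kiryandongo carries 74% of trainees, so the reliance on series at several sites to deal with change over time is not secured by the design.

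A reader might go further and infer that the two small hospitals drop out within the first months, that no multi-site series exists, and that calendar trend is therefore confounded with site. The documents do not support that as a fact. They give no start dates or session calendar by site and no rule that a site stops once its quota is met. Recruiting in order of arrival describes how places are allocated, not when sessions are held. Confounding of site with calendar time follows only if the small sites fill early, which is an assumption.

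**What to change.** 1. Reconcile *Training procedure* with *Sampling methods*: say whether 30 is a target or a maximum, and replace the single range with a number of sessions per site that agrees with 321 / 65 / 47 and with the 3-month interval.
2. Include site in the calendar-time models described in *Statistical analysis*.
3. In *Study strengths and limitations*, limit the time-series claim to Kiryandongo if Jinja and Hoima turn out to give too few or too thin points.

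The cost is wording and one model term, with no added participants or sessions. *Study updates* expected the last participant by 28 November 2023, before publication on 8 February 2024, so changes to how sessions are filled may come too late. The second and third steps remain possible after recruitment, and the first can then report the sessions actually held at each site. The price is a narrower claim if the small sites prove too sparse.
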